## Abstract

**Background:**

There is general agreement that sexuality is a central aspect of human development; it is key in sexual health and reproductive education during adolescence. However, in spite of the existing interventions on this topic and the evidence generated, the inclusion of a gender focus in sexuality is relatively recent and there is little evidence available, thus structured and corroborated interventions with a gender-transforming perspective in sexuality are required.

**Methods:**

We will use a mixed method experimental design with a parallel cluster-randomized trial (GRTs) that will evaluate the effectiveness of a comprehensive gender-transformative intervention of sexual education (ENFOCATE -Focus-on-), which will be complemented with qualitative studies to understand the implementation process. The participants will be 609 10^th^ and 11^th^-grade students. The randomization will be by grade, and the data will be collected at three moments (pre-intervention, post-intervention, and a 3-month follow-up).

**Discussion:**

Comprehensive, gender-focused, and culturally pertinent interventions in sexuality are needed for adolescents of countries with high, middle, and low incomes. These produce better results in terms of sexual health, and including a gender-transformative focus contributes to equity in health. Focus-on is unique since it uses a comprehensive gender-transformative intervention in sexual education that will allow putting into practice a program based both on international evidence and that which arises from the object population. It also uses a culturally-sensitive focus, since it is designed based on the characteristics of the object population; it will allow adapting some activities to the needs of the context in which it is developed.

**Trial registration:**

The study was prospectively registered on June 6, 2023, at ClinicalTrials.gov ID: NCT05896540. Protocol version number 1.0. May 22, 2023.

**Supplementary Information:**

The online version contains supplementary material available at 10.1186/s13063-024-08191-w.

## Background

Adolescence is a sensitive stage in sexual health. Sexual initiation occurs frequently in this stage, which may be associated with greater risks [1]. Adolescents generally face difficulty in accessing information about sexual health and education [2], which is worse for some groups and areas [3]. In Latin America, this difficulty interacts with other factors such as the ethnic group, school dropouts, and income level [4].

One way to approach this topic is to include preventive interventions of sexual education in schools, which is one of the strategies most used to deal with it [5]. This type of intervention may be classified into three large groups: (1) interventions that focus on abstinence, promoting the delay of initiation of sexual relations until marriage, and providing little or no information on methods to prevent pregnancy or sexually transmitted infections (STI) [6]; (2) interventions that focus on risk prevention, which focus specifically on biological aspects of risky behavior in sexuality [7]; and (3) interventions with a comprehensive perspective, which include a holistic vision of sexuality appropriate to the life cycle and whose objective is to equip children and adolescents according to their capacities, providing them with knowledge, abilities, attitudes and values that allow them to develop a positive view of their sexuality [8].

The comprehensive interventions incorporate a teaching process based on cognitive, emotional, physical, and social aspects of sexuality, along with promoting the development of respectful social and sexual relations. They allow considering how their choices affect their well-being and that of others and understanding and guaranteeing the protection of rights throughout their lives. They also provide information about abstinence, how to practice safe sex, and avoid pregnancies and STI [6].

The evidence indicates that the “only abstinence” focus has shown to be less effective than comprehensive sexual education programs, since the latter contribute to retarding the beginning of sexual relations and decrease the number of sexual partners, increase the use of condoms and contraceptives, and promote gender equity [9]. Comprehensive interventions provide precise and appropriate information for different ages, develop abilities, and provide support to cope with the thoughts, feelings, and experiences that accompany sexual maturity [10]. They incorporate biological, psycho-social, and value aspects such as adolescent pregnancy, HIV/STI, sexual diversity, intra-family violence, and masturbation [11]. They also include a perspective of human and gender rights, contributing to increase self-esteem, develop better attitudes towards gender, and strengthen decision-making and communication abilities [6, 11].

However, in spite of the scientific knowledge about the results of comprehensive programs of sexual education, interventions with this focus have been less studied than those of abstinence [12]. Also, not all studies include the gender focus in a consistent manner [13], thus there is a need for more evidence from those studies that do incorporate it [12]. There are also no recent high-quality studies on the elements of its implementation, either in low- and middle-income countries [14] or in the world in general [3].

Interventions in the health area, although they include a gender focus, have difficulty in approaching gender as a determinant of health [15], thus changes in gender roles, relations, and practices need to be included as part of the main purposes of these interventions. This would allow the development of gender-transforming interventions, which consider gender as a factor that affects health, and of actions to approach the components of gender that may damage health [16]; interventions in sexuality are especially relevant, due to the intimate relation between sexual health and gender [17].

Comprehensive gender-transforming interventions in sexual education are especially relevant in Latin America, since the culture is still conservative in this region, and gender norms and attitudes are considered determinants of adolescent sexual health [18]. They are also needed to revert interventions centered on heteronormativity that promote gender inequality [19], distortion in the understanding of sexual orientation, discrimination against peers with different sexual orientations [7], and the development of stereotypes [20].

This kind of approximation has been recommended for scientific research [21], due to the impact that gender may have on health and because it allows for amplifying the external validity of the results [22]. Its use in sexual health is also especially sensitive in adolescents, since the way gender is approached would affect the outcomes of intervention [7].

The challenges mentioned above generated the design of a comprehensive gender-transforming intervention in sexual health education oriented to the adolescent school population called Focus-on, and a mixed experimental design to evaluate its effectiveness and implementation. Focus-on will have a comprehensive gender-transformative perspective, with a participative and reflexive methodology, as well as self-care strategies from abstinence to the practice of safe sex. This intervention will respond to the specific needs of the adolescent population and will be culturally pertinent and situated.

### Objectives of the study

The main objective of this study is to evaluate the effectiveness of a preventive-comprehensive program of sexual education in schools directed to students, using a mixed experimental design [23].

Given that comprehensive programs of sexual health have more effective results in attitudes and knowledge, and that a program that incorporates a gender-transformative perspective contributes to equity in sexual health, we hypothesize that the intervention designed and implemented in the experimental group: (i) will increase their sexuality knowledge level; (ii) will increase their preventive sexual behavior (or intentions); (iii) will favor a gender-positive attitude; and (iv) will decrease internalizing and externalizing problems and attention in mental health. The secondary objective is to examine the implementation intervention process, that is, identify the strengths and obstacles in the real context in which the study intervention is performed, to understand the determinants and strategies of the success of the implementation.

## Methods

### Trial design

We propose a mixed method experimental design [23] with a parallel cluster-randomized trial (GRTs) that will evaluate the efficiency of intervention and implementation of a comprehensive gender-transformative sexual education, along with qualitative studies to understand the implementation process. The results of the intervention will be evaluated after it finishes, and in a 3-month follow-up. Each participant will be sent a link to the questionnaire (web-based survey). Follow-up contact will be done with WhatsApp or telephone calls. The protocol of the study is drafted following the Standard Protocol for a randomized trial of a social or psychological intervention (CONSORT-SPI). Figure 1 is a general flow chart of the procedure (supplementary material 1 includes the SPIRIT checklist).

**Fig. 1 Fig1:**
[figure not shown]
Flow chart of the trial profile of the study

### Participants: eligibility criteria

The intervention will be directed exclusively to students of the 10^th^ and 11^th^ grades who are enrolled in one of the education establishments that depend on the Municipality of Santiago. The inclusion criteria for these schools will be the following: (i) have students of these grades enrolled; (ii) not being an education center oriented to adults or persons deprived of liberty (e.g., closed or semi-closed compounds of Gendarmería de Chile or the National Service for Minors); (iii) have regularity in teaching and learning (for example, schools that were not partially interrupted in 2022 by student manifestations); and (iv) have informed consent of the director. The inclusion criteria for the students will be (i) having 90% or greater attendance in classes: (ii) providing informed consent of voluntary participation; and (iii) having explicit and informed consent of their parents or guardians.

The selected students will be randomly divided into the study and control groups; the intervention will take place in the same schools that the students attend. The assignment to groups will use simple random sampling, performed in two stages. In the first stage, the available schools will be randomly assigned to the study and control groups, while the second stage will randomly select the groups in each school that will participate. The study groups will receive a 10-session intervention in sexual education, covering topics related to preventive sexual conduct, gender equity, and mental health. The control groups will not receive intervention; they will continue with the sexual orientation that each school provides to its students. Sexual orientation is general and is provided by the Ministry of Education. The goal is to evaluate and diagnose the behaviors and reproductive health needs of adolescents, addressing the values adopted regarding the decision to engage in sexual relationships and/or have multiple sexual partners, as well as perceptions of risk.

### Study setting

Interventions will be performed in 10 schools financed by the State located in the commune of Santiago (Metropolitan Region, central Chile), which is the third-most populous commune according to the latest country census.

### Sample size

There are currently 6518 students enrolled in the 10^th^ and 11^th^ grades in State-financed schools in the commune of Santiago. Using a 99% confidence level and a 5% error margin, the sample framework is 605 students, which will be divided into the study and control groups. The statistical power is determined using an analysis of variance with a significance level of 0.05, a sample size of 605 and an expected difference of 0.2 points between groups, which will provide a statistical power of at least 0.8. The 0.2 difference is the smallest reported in previous studies comparing the scores of two groups with the instruments that will be used; it was reported in the analysis of the scores of the scale of ambivalent sexism [24].

The statistical power was calculated using the software G*Power [25]. After making a slight adjustment due to the number of students currently enrolled in each school at each level, the definitive size of the experimental phase of the study will be 609 students.

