### Randomization

The assignment of the participants to the groups will be implemented in a two-stage selection of the students; since there are already existing teaching-learning processes in process in the schools, with their time limitations, we will have to choose entire “courses” (in Chilean secondary schools, a course is a group of about 40 students who have all classes together) rather than choose individual students.

We will establish groups among the schools to compensate for their different sizes; some schools in the commune are much larger than others (four or more courses per grade. Thus, we will divide the schools into two blocks: one with the largest schools and one with the medium- and small-sized schools. In the second stage, courses that meet the inclusion criteria to participate in the study will be selected randomly within each block. Table 1 details the distribution of the samples.

**Table 1 Tab1:** Samples to be selected

	**Study group** **No. of students per grade**		**Control group** **No. of students per grade**		
**School**	*10th grade*	*11th grade*	*10th grade*	*11th grade*	Total
*1*	---	---	31	28	59
*2*	---	---	33	27	60
*3*	---	---	34	34	68
*4*	---	---	26	30	56
*5*	---	---	33	32	65
*6*	29	27	---	---	56
*7*	29	30	---	---	59
*8*	28	29	---	---	57
*9*	25	31	---	---	56
*10*	*40*	*33*	---	---	73
	151	150	157	151	
**Sample totals**	**301**		**308**		**609**

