The result variables of the intervention will be the following: (a) change in knowledge of sexuality manage correctly information on topics related to the biological components of sexuality such as reproduction, prevention of STI and pregnancy, among others; (b) change in preventive sexual behavior, which may be related to (i) behavior or intention to prevent STI and pregnancy, or (ii) sexual abstinence or intention to postpone initiation of sexual life; (c) change in gender attitude related to (i) positive disposition towards persons of different genders and sexual orientation, and (ii) empowering in sexuality of LGBT and female students; (d) change in components of mental health related to sexual health, decrease of internalizing-externalizing symptomology, and improvement in self-efficacy (Table 2). The following instruments will be used:*Knowledge test* [33]. This is a 34-item multiple choice instrument which was designed to evaluate the effectiveness of interventions in sexual education to improve knowledge on sexuality in adolescents; it evaluates areas including pregnancy, STI, physical development, and others. Its reliability is *α* = 0.89.*Ad hoc survey*. It was elaborated by the research team to evaluate the behavior and intention of preventive behavior in sexuality, self-efficacy. and empowerment in sexuality in LGTB and female students. Ad-hoc surveys have been used and reported in other randomized controlled trial of interventions in sexual health (e.g.. Coyle [34], Goesling [35]. and Yakubu [36]). This survey will follow the guidelines developed by Manaseri [37] and Jirapongsuwan [38].*Scale for detection of sexism in adolescents (DSA)* [39]. This is an instrument of 26 items developed for adolescents. It evaluates sexism (attitude of superiority towards women), differentiating between hostile and benevolent sexism. The response scale for the items is a Likert type with six alternatives (from 1 = disagree completely to 6 = agree completely). Its reliability is *α* = 0.881.*Scale of negative attitudes toward trans persons (NATP)* [40]. It measures attitude as an expression of prejudice towards trans persons. It has nine items with a Likert scale with five response options, from 1 = disagree completely to 5 = agree completely. Its reliability is *α* = 0.886.*Short version of modern homophobia scale* [41]. It measures homophobic attitudes in the dimensions of personal discomfort, institutional, and deviation/changeability. It is composed of 46 items that evaluate attitudes towards lesbians and gays on a Likert scale of 1–5. Its reliability is *α* = 0.80.*Pediatric symptom checklist (PSC-17)* [42]. This is an abbreviated version of the 35-item PSC [43]. It evaluates general psychosocial functioning, detecting emotional and behavioral difficulties in children and adolescents [44]. Its reliability is *α* = 0.72. PSC-17 is self-administered by adolescents, evaluating the existence of internalizing difficulties (e.g., despair and sadness), externalizing difficulties (e.g., difficulties in social relations such as disobedience of norms and fights with others), and attention difficulties (e.g., difficulty in concentration -60,66-). As in other studies (e.g., Penner [45]), this instrument will be used to evaluate the adolescents’ mental health. The baseline and follow-up evaluations will be obtained confidentially, and be recorded in files managed by the team responsible for the study.

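### The stated power of at least 0.8 treats 605 students as independent although ten whole schools are allocated, and it cannot be verified because the 0.2 has no SD or defined scale

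*Protocol article*

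**What the plan says.** The Sample size section first fixes the number of students by a survey-precision rule: "Using a 99% confidence level and a 5% error margin, the sample framework is 605 students". It then makes a power statement at that number. The method is given as "The statistical power is determined using an analysis of variance with a significance level of 0.05", and the result as "a sample size of 605 and an expected difference of 0.2 points between groups, which will provide a statistical power of at least 0.8". The software is G*Power. The 0.2 is described as the smallest difference found in earlier two-group comparisons using the trial's instruments, and of its source the section says "it was reported in the analysis of the scores of the scale of ambivalent sexism". After adjustment to enrolment, the final number is 609.

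Elsewhere the article describes a cluster design. Trial design calls it a parallel cluster-randomised trial. The eligibility section assigns schools to arms at random in a first stage and selects groups within schools in a second. Study setting gives ten schools. Randomization explains that whole courses are taken "rather than choose individual students", and Table 1 places each school entirely in one arm: five control schools (308 students) and five study schools (301).

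**The concern.** Students in one school share teachers, peers and, in the study arm, the staff who deliver the sessions. When whole schools are allocated, between-school variation enters the error of the treatment comparison, and there are only ten schools from which to estimate it. A calculation whose inputs are alpha, total students and a difference leaves both facts out, so it describes a different design.

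The second problem is that the effect size is not defined. A difference in points has no power attached to it until an SD is given, and the G*Power ANOVA module takes Cohen's f rather than a difference in points. The reader cannot tell which quantity was entered.

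At stake is the reading of a null result. If the trial is believed to have 80% power, a null finding will be taken as evidence against the programme. That inference is unsafe if the true power is materially lower.

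**Working it through.** **Inputs from the article.** Alpha 0.05; N = 605 for the power claim; 301 and 308 students in Table 1; ten schools with a mean of 609/10 = 60.9 students (range 56 to 73); population 6518.

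**Assumptions, not in the article.** Two-sided test; school ICC 0.01, 0.02 or 0.05; three readings of the 0.2.

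**1. Where 605 comes from.** n0 = z² × 0.25 / 0.05², then n = n0 / (1 + (n0 − 1)/6518). With z = 2.58, n0 = 665.64 and n = 604.05, which rounds up to 605. With z = 2.576, n = 602.3. So 605 reproduces, as a sample size for estimating a proportion.

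**2. The power claim with independent students (302 and 303).** ncp = d / √(1/302 + 1/303), noncentral t on 603 df.
- 0.2 as Cohen's d: ncp = 2.460, power 0.690. Reaching 0.80 would need 394 per arm, 788 in all.
- 0.2 as raw points: power reaches 0.80 when d = 0.228, so the claim holds if the SD is at most 0.2/0.228 = 0.877 points.
- 0.2 as Cohen's f with two groups (d = 2f = 0.4): power 0.998.

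**3. The same readings with schools allocated.** DEFF = 1 + (60.9 − 1) × ICC, which is 1.599, 2.198 and 3.995 at the three ICCs. ncp = d / √(DEFF × (1/301 + 1/308)), with √(1/301 + 1/308) = 0.0810. The reference is t on 10 − 2 = 8 df, critical value 2.306. For d = 0.2 and ICC 0.01, ncp = 1.951.

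| Reading of 0.2 | Independent students | ICC 0.01 | ICC 0.02 | ICC 0.05 |
|---|---|---|---|---|
| Cohen's d = 0.2 | 0.69 | 0.41 | 0.31 | 0.19 |
| Raw 0.2, SD 0.877 | 0.80 | 0.50 | 0.39 | 0.24 |
| Cohen's f = 0.2 (d = 0.4) | 0.998 | 0.93 | 0.83 | 0.58 |

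The middle row uses the largest SD at which the individual-level claim is still true. With a smaller SD of 0.7, individual-level power is 0.94 and clustered power 0.69, 0.55 and 0.34.

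**4. Detectable difference.** On 8 df, 80% power needs ncp of about 3.20. The detectable d is therefore 3.20 × 0.0810 × √DEFF = 0.259 × √DEFF, which is 0.33, 0.38 and 0.52 at ICC 0.01, 0.02 and 0.05. On the f reading, 0.8 holds while √DEFF ≤ 0.4/0.259 = 1.54, so DEFF ≤ 2.38 and ICC ≤ 1.38/59.9 = 0.023.

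**The case against.** The strongest reply is that nothing in the section is shown to be miscalculated. The 605 reproduces, and several ordinary readings give 0.8 or nearly so for independent students: f = 0.2 (0.998), raw 0.2 with an SD up to 0.877, a one-sided test of d = 0.2 (0.79), or a repeated-measures between-group test with f = 0.1, three measures and an assumed correlation of 0.5 (0.85). A reader might infer that the claimed power is simply not delivered, or that the true power is 0.2 to 0.4. The documents do not support either as a flat statement: both need the 0.2 to be Cohen's d, and the second also needs an assumed ICC of 0.01 to 0.05. This part of the reply stands.

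The clustered figures also give no credit for the two size blocks or the baseline measurement, and either could raise power. If the 20 school-by-grade cells were the clusters, as the Abstract's mention of randomisation by grade might suggest, d = 0.2 would give 0.54, 0.46 and 0.32 on 18 df. Table 1, however, shows schools undivided between arms.

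Three further inferences go too far:
- That the 0.2 belongs to no outcome in the trial. No listed instrument is called an ambivalent sexism scale, but the DSA separates hostile from benevolent sexism, so the label may be loose. Only the cited source would settle it.
- That the survey formula invalidates the power. It fixes N; the power check at that N is separate.
- That the margin of 609 − 605 = 4 students is decisive. With ten clusters, a 20% loss in both arms moves d = 0.2 at ICC 0.01 only from 0.41 to 0.36.

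It could also be said that clustering is left to an analysis plan not shown. That does not answer the point: the article publishes a complete calculation with inputs, software and result, and the allocation unit is absent from it.

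**Conclusion.** Wrong as written: the stated power is for individually allocated students, and this trial allocates ten schools. It is also unverifiable, because the scale and SD of the 0.2 are missing.

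The size of the shortfall depends on what 0.2 means and on the ICC. Across the three tabulated readings and assumed ICCs of 0.01 to 0.05, unadjusted power runs from 0.19 to 0.93. It stays at or above 0.8 only on the Cohen's f reading and only up to an ICC of about 0.02. On the d reading the claim fails before clustering is considered. For raw points at the largest SD compatible with the claim, it fails once schools are the unit: even at ICC zero, 8 df alone brings 0.80 down to 0.69. A smaller raw SD would leave more room, so the documents do not fix a single true power.

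**What to change.** Keep 609 students and rewrite the power paragraph:
- Define the 0.2: which outcome, on what scale, with what SD, and whether it is raw, d or f.
- State an assumed school ICC with a range, and its source.
- Report power and the minimum detectable standardised difference for five against five schools on 8 df, at the number of students expected to be analysable, with and without baseline adjustment. That number should allow for the planned removal of students who miss more than 30% of sessions.
- Stop presenting the survey-precision formula as the justification for a two-arm comparison.
- Say which listed instrument the ambivalent sexism difference refers to.

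The cost is one rewritten paragraph and a stated power that will probably be less favourable. No extra students or schools are required.

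### The stated power of at least 0.8 comes from 605 students treated as independent, with no SD or ICC, so it does not describe a trial that allocates ten schools

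*Protocol article*

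**What the plan says.** In the protocol article, Sample size, the number of students comes from a survey-precision rule: "Using a 99% confidence level and a 5% error margin, the sample framework is 605 students". That number is then put into a power statement based on an "analysis of variance with a significance level of 0.05", run in G*Power: "a sample size of 605 and an expected difference of 0.2 points between groups, which will provide a statistical power of at least 0.8". This value is described as the smallest difference found in earlier studies with the instruments, and "it was reported in the analysis of the scores of the scale of ambivalent sexism". The final size is 609 after adjustment to enrolment.

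The design is described elsewhere. Trial design calls it a parallel cluster-randomized trial. Participants: eligibility criteria says that in the first stage "the available schools will be randomly assigned to the study and control groups". Study setting gives ten schools. Randomization explains that whole courses must be taken "rather than choose individual students". Table 1 places every school entirely in one arm: five control schools (308 students) and five study schools (301 students), with 56 to 73 students per school. The Abstract says randomization is by grade. In Table 1, however, both grades of each school sit in the same arm, so the allocated unit there is the school.

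**The concern.** When whole schools are allocated, students of one school share teachers, climate and intake. Their scores are correlated, and the comparison between arms rests on five school means against five. Power then depends on the between-school variance and on 10 − 2 = 8 degrees of freedom, not on 605 separate students. The power statement contains neither quantity. It also gives the target difference in raw points without an SD, so the standardised effect is not fixed.

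What is at stake is how a null result is read. A reader told that power is at least 0.8 expects to miss the planned difference at most 20% of the time. If that difference is 0.2 SD, the miss rate would be about 60% to 81% at the ICCs assumed below, and a null result could be taken as evidence of no effect when it is not.

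**Working it through.** **Inputs from the article:** alpha 0.05; difference 0.2 points; N = 605 for power and 609 final; ten schools, 5 against 5; mean size 609/10 = 60.9.

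**Assumptions, not in the article:** two-sided test; ICC of 0, 0.01, 0.02 and 0.05; SD of 1 point (0.2 SD) or 0.5 points (0.4 SD); unadjusted comparison at one time point.

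**1. Origin of 605.** Taking z = 2.58, proportion 0.5 and margin 0.05, n0 = 2.58² × 0.25 / 0.05² = 665.6. With the finite-population correction, 665.6 / (1 + 664.6/6518) = 604. (With z = 2.576 the result is 602.) The 605 is essentially reproduced, and it is a precision figure for a simple random sample of students.

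**2. The stated power, ignoring clustering.**
- One-way ANOVA, two groups, 0.2 SD: noncentrality 605 × 0.2² / 4 = 6.05 on (1, 603) df, power 0.69.
- Between-groups test with three measurements, f = 0.1, correlation 0.5: noncentrality 0.1² × 605 × 3 / (1 + 2 × 0.5) = 9.08, power 0.85. At correlation 0.3 and 0.7 it is 0.92 and 0.78.
- One-way ANOVA with 0.2 entered as Cohen's f: for two equal groups d = 2f = 0.4, power 0.998.

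Depending on the ANOVA and the unit of the 0.2, the result is below, near or far above 0.8. The article does not say which was entered.

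**3. Power with ten schools.** Design effect = 1 + (60.9 − 1) × ICC. Noncentrality = d² × 609 / (4 × design effect), referred to F with (1, 8) df. For example, at ICC 0.02 and d = 0.2 the design effect is 2.20 and the noncentrality is 0.04 × 609 / (4 × 2.198) = 2.77, which gives power 0.31.

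| ICC (assumed) | Design effect | Power, 0.2 SD | Power, 0.4 SD | Detectable at 80% |
|---|---|---|---|---|
| 0 | 1.0 | 0.58 | 0.99 | 0.26 SD |
| 0.01 | 1.6 | 0.40 | 0.93 | 0.33 SD |
| 0.02 | 2.2 | 0.31 | 0.83 | 0.39 SD |
| 0.05 | 4.0 | 0.19 | 0.58 | 0.52 SD |

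Using the individual school sizes in Table 1 instead of the mean changes these powers by less than 0.01.

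**4. SD at which 0.2 points gives power 0.8.** Dividing 0.2 by the unrounded detectable difference (0.328, 0.385, 0.519) gives an SD of at most about 0.61, 0.52 and 0.39 points at ICC 0.01, 0.02 and 0.05.

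**5. Effect of baseline adjustment.** If baseline explained 40% of the variance at both levels, power for 0.2 SD would be 0.60, 0.47 and 0.29 at ICC 0.01, 0.02 and 0.05. Detectable differences shrink by √0.6 to about 0.25, 0.30 and 0.40 SD. The 40% is illustrative, and Analytical methods describes no baseline covariate.

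**The case against.** The strongest reply is that the shortfall is not established, because the article says "an expected difference of 0.2 points between groups" and never says SD. This stands. The source study is not available here, so the standardised difference is unknown. If the outcome SD were about 0.5 points, or if 0.2 was entered as Cohen's f, clustered power would be 0.93 and 0.83 at ICC 0.01 and 0.02, above the stated level. A reader might infer that 0.8 can be reached only if students are independent and the SD is 0.88 points or less. The 0.4 SD column shows otherwise: 0.8 is reachable with clustering if the SD is small enough.

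A second reply concerns the unclustered calculation. A reader might infer from the 0.69 that the figure is wrong even for independent students. That holds for a single-time one-way ANOVA at 0.2 SD, but Analytical methods also plans a factorial ANOVA over three evaluations, and a three-measurement between-groups test can give 0.85. What the article supports is that the figure cannot be verified, not that it is wrong under independence.

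A third reply is that an article condenses its protocol. That would excuse an omitted derivation. Here, though, the article prints the method, sample size, alpha, difference, software and result, and none of these reflects the cluster allocation it also prints. The ICC values are assumptions, but at 0.2 SD in an unadjusted single-time comparison no ICC rescues the claim, since power is 0.58 at ICC 0.

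**Conclusion.** The point holds in a conditional form. The statement "which will provide a statistical power of at least 0.8" was derived for individually sampled students and does not describe a comparison of five schools with five. This follows from the article alone and needs no assumed ICC.

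The size of the error does need assumptions. Read as 0.2 SD, unadjusted, two-sided 0.05 with 8 df, power is about 0.40 to 0.19 for ICC 0.01 to 0.05, and the trial could detect about 0.33 to 0.52 SD with 80% power. Read as 0.4 SD, power is 0.93 to 0.58 over the same range, so the claim survives at ICC 0.01 and 0.02 and fails at 0.05. It would be too strong to say outright that the trial has power of 0.2 to 0.4, or that differences of the planned size would usually be missed. Both depend on an SD that the article does not give. It remains a necessary correction, because this figure is the article's only statement of what the sample can detect.

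**What to change.** Recompute and restate the power paragraph for the actual design: ten schools of about 61 students, five per arm, with 8 degrees of freedom. State the scale to which the 0.2 points refers and its SD, a range of ICCs, the type of ANOVA or model assumed, and any gain claimed from repeated or baseline measurements with the correlation behind it. Report the resulting power and the difference detectable with 80% power in place of the present figure. Reconcile the Abstract's statement that randomization is by grade with the school-level allocation in Participants: eligibility criteria and Table 1, since the calculation depends on the unit.

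The cost is one rewritten paragraph and, on most readings, a less favourable stated figure. No additional schools or students are required.
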